### Study populations

For primary quantitative outcomes, the study population will include adult patients (≥ 18 years of age) who qualify for a diagnosis of hypertension, type II diabetes, and/or COPD, according to WHO-PEN guidelines, and are engaged in longitudinal care by Nyaya Health Nepal’s team in Achham and Dolakha. The study will limit enrollment to the catchment areas served by both the facility-level and CHW-level services deployed by Nyaya Health Nepal. Study participants will be initially enrolled during facility-based visits at Bayalpata Hospital and Charikot Primary Health Care Center prior to the completion of intervention roll-out, and are considered engaged in longitudinal care if they have at least one follow-up hospital visit after 12 months of their initial visit. Digital health records that link between the facility-based EHR and the CHWs’ mobile-phone applications will be utilized to share patient data across settings, when available. CHWs can identify potential patients in the community and refer them to the facility for diagnosis confirmation, following which they could be included in the study. Patients’ receipt of care will not be contingent upon their enrollment in the study; all patients will continue to receive care per routine service delivery. This represents an exhaustive convenience sampling method as all eligible patients identified at Bayalpata Hospital and Charikot Primary Health Care Center may be enrolled in the study. Exclusion criteria are individuals planning to migrate from the study area prior to 12 months of exposure to the intervention, or individuals explicitly requesting exclusion from the study or declining to consent (see Additional file 3) for the study.

For implementation components, staff members, patients, community leaders, and government officials will be approached for key-informant interviews (KIIs) and focus group discussions (FGDs), as described in the following.

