### Study design

This is a prospective, mixed-methods type 2 hybrid effectiveness-implementation study to evaluate an integrated NCD care management intervention. We plan to apply both qualitative and quantitative methods in a complementary manner [79], in order to meaningfully assess both patient-level and population-level outcomes and the effectiveness of the implementation strategy. We will study the intervention’s impact on patients’ disease management outcomes after 12 months of being enrolled in NCD care using a pre–post design across both sites:
We will study the implementation of the intervention utilizing both quantitative and qualitative methods applying the RE-AIM (Reach, Effectiveness, Adoption, Implementation, Maintenance) framework [80].

Data collection is developed and integrated within the routine course of delivering care, which is an ethical, acceptable, and affordable approach in this setting. See Fig. 1 for a trial flowchart and Additional file 4 for a SPIRIT research reporting checklist. It is not feasible nor ethically acceptable to obtain data on a comparison (control) group in this population. Given the lack of national or local NCD systems, no data are available from other sources prior to the start of the study.

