### Sampling strategy and power calculations

We will use exhaustive convenience sampling to screen all eligible patients seen across two facilities over a 12-month period into the analysis cohort. Based on historical formative data of patient volume seen at these two facilities, and accounting for an expected 30% attrition rate, we conservatively expect that at least 1000 patients will be eligible for enrollment into the cohort.

With this conservative number of 1000 as our expected sample size based on this convenience sampling, we conducted power calculations to determine the statistical power to detect a change in the “at-goal” status. We calculate power based on a simplified design to compare paired proportions using a two-sided McNemar’s test with an 0.05 type I error (α) level. The primary outcome is the proportion of patients who achieve their NCD control target (“at-goal status”) after 12 months of being engaged in care. We used SAS version 9.4 (Cary, NC, USA) to estimate power to detect a 5% difference between discordant proportions; that is, proportions of patients whose “at-goal” status changed from “not at-goal” at baseline to “at-goal” at follow-up, and vice versa, in multiple scenarios where the total proportion of discordant patients ranged from 10 to 40% of all patients. Based on these assumptions, our power to detect a 5% difference in the discordant pairs is 69%, when the total discordant proportion is 40%, and the power is 99% when 10% of all patients are discordant.

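### Patients who enter at diagnosis are selected on the outcome measure, so the uncontrolled pre–post comparison counts regression to the mean as improvement

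*Protocol article*

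**What the plan says.** **Entry.** Under Study populations, eligible adults are those "who qualify for a diagnosis of hypertension, type II diabetes, and/or COPD, according to WHO-PEN guidelines". "Study participants will be initially enrolled during facility-based visits at Bayalpata Hospital and Charikot Primary Health Care Center". Community health workers may find possible cases and "refer them to the facility for diagnosis confirmation, following which they could be included in the study". Study setting lists proactive case detection among their services, so new diagnosis is an intended way in.

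**Time zero.** Engagement in care requires "at least one follow-up hospital visit after 12 months of their initial visit". No repeat, averaged or later baseline reading is defined.

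**Comparison.** Study design has the effect judged "after 12 months of being enrolled in NCD care using a pre–post design across both sites". It adds: "It is not feasible nor ethically acceptable to obtain data on a comparison (control) group in this population", and that "no data are available from other sources prior to the start of the study".

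**Outcome.** Table 2 defines at-goal status by blood pressure for hypertension, by A1c or fasting glucose for diabetes, and by exacerbation criteria for COPD.

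**Analysis.** Sampling strategy and power calculations uses a "simplified design to compare paired proportions using a two-sided" McNemar test, for power only. Analysis for Specific Aim 1 names conditional multivariable logistic regression. Its covariates are demographics, municipality, district, distance to hospital and number of encounters. It hypothesises that the intervention will raise at-goal status in the combined disease cohorts by 10%.

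**The concern.** Blood pressure and glucose are the measures on which hypertension and diabetes are diagnosed, and also the measures on which success is scored. A patient who enters because such a reading was high tends to read lower next time, treated or not. If the reading at entry is also the baseline, movement toward goal is favoured before any intervention effect, and the null of equal movement in both directions is false for these patients. COPD patients are affected only if they present while their symptoms are worsening.

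Nothing in the design absorbs this. There is no concurrent or historical comparison, the listed covariates do not correct it, and new and established patients are pooled. Both the type I error of the primary comparison and the wording of the effectiveness claim are at stake.

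**Working it through.** **1. The protocol's own power figures.** McNemar power is approximately Φ[(d√n − z√ψ)/√(ψ − d²)], where d is the difference between the discordant proportions, ψ their total and z = 1.96. From the protocol, n = 1000, d = 0.05 and ψ = 0.10 to 0.40.

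- ψ = 0.40: (1.581 − 1.240)/0.630 = 0.542, power 70.6%. The exact test gives 69.0%; the protocol states 69%.
- ψ = 0.10: (1.581 − 0.620)/0.312 = 3.08, power 99.9%; the protocol states 99%.

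The stated figures reproduce to within a point. The power arithmetic is not the problem.

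**2. Drift with no true change.** The protocol gives no blood pressure distribution, visit-to-visit correlation or diagnostic cut-off. I assume systolic mean 130, SD 18, correlation r between visits and entry at 140 or more. The goal of 130 is the systolic part of the Table 2 default. With one qualifying reading,

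P(X₂ < 130 | X₁ ≥ 140) = [Φ(0) − Φ₂(0.556, 0; r)] / [1 − Φ(0.556)], where 0.556 = (140 − 130)/18.

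The two-reading column is simulated under the same assumptions.

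| r | One reading must qualify | Two readings must qualify |
|---|---|---|
| 0.6 | 20% | 11% |
| 0.7 | 15% | 7% |
| 0.8 | 9% | 4% |

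**3. The choice of baseline drives this.** A second simulation assumed true systolic pressure with mean 128 and SD 16, visit-to-visit SD 10, one qualifying reading of 140 or more, and no intervention effect. With the qualifying reading as baseline, 15.6% moved to goal and none moved away. With a separate reading as baseline, 9.5% moved each way, so the net change was zero.

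**4. Effect on the pooled comparison.** Let f be the share newly diagnosed and q their drift to goal with zero effect. Assume the other patients are 20% discordant and symmetric. Then

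- moving to goal = f·q + (1 − f)·0.10
- moving away = (1 − f)·0.10
- spurious net gain = f·q

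For f = 0.20 and q = 0.10, the movements are 0.10 and 0.08, so d = 0.02 and ψ = 0.18. The upper tail is Φ[(0.632 − 0.832)/0.424] = 0.319 and the lower tail is negligible, so the rejection rate is 32%.

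False-positive rate at nominal 5%, n = 1000:

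| Share new | Drift 5 points | Drift 10 points | Drift 15 points |
|---|---|---|---|
| 10% | 7% | 11% | 19% |
| 20% | 12% | 32% | 59% |
| 30% | 23% | 63% | 91% |
| 50% | 61% | 98% | near 100% |

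The 98% is 99% by simulation. At 50% new and a 10-point drift, the spurious gain is 0.50 × 10 = 5 points, the difference used in the power calculation.

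**5. Carry-over to the planned model.** Conditional logistic regression matched on patient estimates the pre–post effect from the same discordant pairs, so it inherits the bias. The protocol does not state the matching unit.

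**The case against.** - **The baseline reading is not named.** The protocol nowhere says that the diagnosing reading is the baseline; it says inclusion follows confirmation. The schedule figure is not shown, and a full protocol or analysis plan may settle it. This stands as a limit: the protocol offers no other baseline, but the point rests on that reading.
- **McNemar is not the stated primary analysis.** True. The concern reaches the planned regression only if it is matched on patient.
- **A certain false positive.** A reader might infer that the primary test will be significant whatever the intervention does, since with movement in one direction only, six changed patients give an exact p of 2 × 0.5⁶ = 0.03. The documents do not support this. Established patients are pooled in and move both ways, some NCD care has been given in Achham since 2008, and the share of new patients is not stated. At 10% new, the false-positive rate is 7–19%, not near one.
- **New patients can only improve.** Also too strong. Hypertension goals may be tailored, diabetes is at goal on either of two measures, and COPD is not scored on its diagnostic basis. The full 130/80 goal would also lower the share of systolic entrants who drift to goal.
- **Restricting the test to previously diagnosed patients.** This has its own bias. Trial status puts deployment from July 2018 to January 2020 and enrolment from February 2020, so these patients may already have been exposed.

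**Conclusion.** The concern holds as a bias of uncertain size. Diagnosis-triggered entry, a clock that starts at the initial visit, a within-patient comparison on the diagnostic measure and the absence of any control together let regression to the mean count as improvement.

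The pooled spurious gain is the share newly diagnosed times their drift. At 10 points of drift that is 1 point if 10% are new and 5 points if 50% are new, with false-positive rates of about 11% and 98%. These sizes rest on assumed blood pressure variability, an assumed entry threshold, an assumed share of new patients and symmetric 20% discordance in the rest. They also require that the entry reading serves as baseline. The mechanism is clearest for hypertension and diabetes.

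The supported conclusion is an inflated type I error and a pre–post change that cannot be attributed in full to the intervention. It does not follow that the trial is bound to be positive.

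**What to change.** 1. Keep the full cohort, and state which reading is the baseline.
2. Flag newly versus previously diagnosed patients from the diagnosis date in the electronic health record. Report the pre–post change for each group beside the pooled result.
3. For newly diagnosed patients, report the 12-month at-goal proportion with a 95% confidence interval, and do not attribute their pre–post change to the intervention.
4. Where the record holds a second reading taken before treatment, use it as baseline in a sensitivity analysis. A first reading after diagnosis will not do if treatment has already started.
5. State that previously diagnosed patients may have been exposed since July 2018, so that their change may understate the effect.

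**Cost.** One derived flag and a stratified report, with no new data collection. Precision falls within each group, so power should also be stated for the previously diagnosed group. By the formula in step 1 of the working, with a 5-point difference and 40% discordant, power falls from 71% at 1000 patients to 61% at 800 and 42% at 500. With 10% discordant it stays at 99% and 94% for those numbers.

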### Study design

This is a prospective, mixed-methods type 2 hybrid effectiveness-implementation study to evaluate an integrated NCD care management intervention. We plan to apply both qualitative and quantitative methods in a complementary manner [79], in order to meaningfully assess both patient-level and population-level outcomes and the effectiveness of the implementation strategy. We will study the intervention’s impact on patients’ disease management outcomes after 12 months of being enrolled in NCD care using a pre–post design across both sites:
We will study the implementation of the intervention utilizing both quantitative and qualitative methods applying the RE-AIM (Reach, Effectiveness, Adoption, Implementation, Maintenance) framework [80].

Data collection is developed and integrated within the routine course of delivering care, which is an ethical, acceptable, and affordable approach in this setting. See Fig. 1 for a trial flowchart and Additional file 4 for a SPIRIT research reporting checklist. It is not feasible nor ethically acceptable to obtain data on a comparison (control) group in this population. Given the lack of national or local NCD systems, no data are available from other sources prior to the start of the study.

**Fig. 1 Fig1:**
[figure not shown]
Standard Protocol Items: Recommendations for Interventional Trials (SPIRIT) figure. [81] Recommended content can be displayed using various schematic formats. See SPIRIT 2013 Explanation and Elaboration for examples from protocols. **List specific timepoints in this row

### Study outcomes

The study has two specific aims: effectiveness (Specific Aim 1) and implementation (Specific Aim 2), as detailed in Table 1. For Specific Aim 1, the primary outcome will be the proportion of patients who meet disease-specific, evidence-based control measures at the completion of their initial 12 months engaged in treatment. These “at-goal” metrics aim to serve as simplified measures to assess disease control status, recognizing the limitations associated with multiple disease-specific metrics in settings like rural Nepal, especially for patients with multiple comorbid conditions. These are presented in Table 2.

**Table 1 Tab1:** Metrics for Specific Aim 1 (efficacy) and Specific Aim 2 (implementation)

Aim	Outcome/RE-AIM element	Indicator	Definition
Specific Aim 1: efficacy	Primary outcome: control of NCD conditions	Condition-specific “at-goal” metrics	% of enrolled NCD patients achieving “at-goal” status (Table 2), at completion of the study period
	Secondary outcome 1: tobacco use	Tobacco use status	% of enrolled NCD patients who were using tobacco at enrollment who are nonusers or who have reduced by > 50% their tobacco intake, at completion of the study period
	Secondary outcome 2: alcohol use	Alcohol use status	% of enrolled NCD patients who were alcohol drinkers at enrollment who are nondrinkers or who have reduced by > 50% alcohol intake, at completion of the study period
Specific Aim 2: implementation	Reach	Home visit coverage	% of enrolled NCD patients having a CHW home visit, measured monthly
		Clinic visit coverage	% of enrolled NCD patients having an MLP visit at the clinic, measured monthly according to the patients indicated to be seen that month based on protocol-based guidelines
		Demographic, geographic barriers and facilitators	% of enrolled NCD patients whose CHW has GPS-mapped their households, describing barriers/facilitators to individuals’ access, and identifying contributors to variation/inequities
		Loss to follow-up	% of patients, stratified by demographic data and NCD conditions, who are lost to follow-up after enrollment
		Monthly patient touch-points	Number of monthly per-patient touch-points, including interactions by both MLPs and CHWs
	Efficacy	Evidence-based hypertension management	% of enrolled hypertension patients in accordance with evidence-based recommendations, as prescribed by clinical algorithms, assessed quarterly by EHR audits
		Evidence-based diabetes management	% of enrolled diabetes patients in accordance with evidence-based recommendations, as prescribed by clinical algorithms, assessed quarterly by EHR audits
		Evidence-based COPD management	% of enrolled COPD patients in accordance with evidence-based recommendations, as prescribed by clinical algorithms, assessed quarterly by EHR audits
	Adoption	Village-cluster adoption	% of intended village clusters receiving intervention
		Timely adoption	% of intended village clusters rolling-out intervention within 3 months of schedule, according to local governance decisions to roll-out the intervention
		CHW adoption	% of CHWs trained in intervention implementation within the first 6 months % of trained CHWs retained in their positions at completion of the study period
		MLP adoption	% of MLPs trained in intervention implementation % of trained MLPs retained in their positions at completion of the study period
	Implementation	Care integration	% of all NCD patients enrolled at the facilities seen by CHWs at home within the first month
		CHW supervision model	% of scheduled CHW supervision field visits completed, stratified by CHN and district, measured quarterly % of scheduled quarterly data review meetings held with CHWs and CHNs, measured quarterly
		CHW home visit fidelity	% of enrolled NCD patients with 100% of algorithm-indicated home visits received % of topics included at each session as dictated by the condition-specific algorithms, assessed during the CHW supervision field visits by CHNs, measured quarterly
		Referrals	% of patients appropriately referred to MLP care as indicated by the clinical algorithms, assessed during the CHW supervision field visits by CHNs, measured quarterly % of patients referred by CHWs seen by MLPs within the prescribed time window according to the clinical algorithms (e.g., 24 h, 72 h, 1 week), measured quarterly
		MLP supervision model	% of enrolled NCD patients appropriately referred to see a physician by MLPs as indicated by the clinical algorithms, assessed during monthly physician supervision sessions, measured quarterly
		MLP visit fidelity	% of enrolled NCD patients with 100% of algorithm-indicated facility visits received, assessed during monthly physician supervision sessions, measured quarterly % of diagnostic, treatment, and counseling topics included at each session as dictated by the condition-specific algorithms, assessed during monthly physician supervision sessions, measured quarterly
		Implementation challenges	Exploratory and hypothesis-generating as revealed through FGDs and KIIs with CHWs, CHNs, MLPs, physicians, patients, and other relevant community stakeholders
	Maintenance	Total intervention cost	Cost of each intervention component and total costs using the Joint Learning Network costing methodology
		Intervention initiation costs	% breakdown of initial (one-time) costs for intervention (training, equipment, etc.)
		Intervention maintenance costs	% breakdown of maintenance (recurring) costs (ongoing training, personnel, materials, and other)
		Facility vs. community costs	% of costs of healthcare divided between facility level and community level
		Geographic cost variation	Characterization of variance in costs between village clusters and districts within the intervention catchment area
		Out-of-pocket patient costs	% costs of healthcare divided between facility level and community level
		Integrated intervention cost-effectiveness analysis	Pre/post-intervention marginal effectiveness for primary outcomes
		Cost per unit	Intervention cost per enrolled patient Intervention cost per capita Projected cost to scale intervention nationally, based on known incidence and prevalence of each condition

*CHN* community health nurse, *CHW* community health worker, *COPD* chronic obstructive pulmonary disease, *EHR* electronic health record, *FGD* focus group discussion, *GPS* Global Positioning System, *KII* key-informant interview, *MLP* mid-level practitioner, *NCD* Noncommunicable disease, *RE-AIM* Reach, Effectiveness, Adoption, Implementation, Maintenance

**Table 2 Tab2:** Clinical definitions of “at-goal” status for each intervention condition

Noncommunicable disease	Management metric	“At-goal” definition
Type II diabetes mellitus	Hemoglobin A1c OR fasting blood sugar	Hemoglobin A1c < 7.5 OR fasting blood sugar < 130 mg/dl^a^
Hypertension	Blood pressure	Blood pressure < 130/80 mmHg or patient-tailored goal per risk stratification^b^
Chronic obstructive pulmonary disease	Exacerbation status	≤ 1/3 Anthonisen criteria^c^

^a^The 2018 American Diabetes Association guidelines [82] call for a goal A1c < 7% for most patients or A1c < 8% in “patients with a history of severe hypoglycemia, limited life expectancy, advanced microvascular or macrovascular complications, extensive comorbid conditions, or long-standing diabetes in whom the goal is difficult to achieve despite diabetes self-management education, appropriate glucose monitoring, and effective doses of multiple glucose-lowering agents including insulin.” For our intervention, we established 7.5% as our goal to pragmatically accommodate both populations

^b^Based on the 2017 American College of Cardiology and American Heart Association guidelines [83], we established < 130/80 mmHg as a default goal, with patient-tailored goals for select patients (≥ 65 years of age, multiple comorbidities, limited life expectancy, clinical judgment, patient preference)

^c^The 2017 update to the GOLD guidelines [84] define chronic obstructive pulmonary disease exacerbation as an “acute worsening of respiratory symptoms that results in additional therapy.” We used the Anthonisen criteria of worsening sputum volume, sputum purulence, and increased dyspnea to define the “worsening of respiratory symptoms” specified in the GOLD guidelines. We established a threshold of no more than one Anthonisen criterion as a pragmatic tool for determining clinical status

Secondary outcomes for Specific Aim 1 will include the following. We will assess the individual “at-goal” rates per condition. We will assess the persistence of the intervention for the subset of patients for whom we have the data (i.e., those enrolled within 12 months of the start of the study) on their 24 months’ outcome. Additionally, we will examine the tobacco and alcohol status of enrolled patients, specifically focusing on the proportion of patients who were tobacco users and/or alcohol drinkers at the time of enrollment who have stopped all tobacco and/or alcohol intake, or reduced their intake by > 50%, by the completion of the study period (Table 1).

For Specific Aim 2, the RE-AIM framework will be utilized to assess the implementation of the study intervention, with RE-AIM metrics as presented in Table 1.

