### Data collection

#### Quantitative data

Quantitative data for patient outcomes will be extracted from the facility-based EHR and the CHW’s mobile-phone application (Additional file 5), and will be used to assess Specific Aims 1 and 2. (Table 1) All implementation-related data for evaluating the performance of MLPs and CHWs (Table 1) will be collected by the responsible MLP and CHW supervisors in digitized checklists within the EHR and mobile-phone application. Access to protected health information will be controlled and defined by user access groups according to clinician status. Data to be analyzed will be extracted via secure data queries from the EHR system in an aggregate, partially de-identified form, with external researchers signing a data-sharing and use agreement prior to analysis. Cleaned, de-identified datasets will be made publicly available via a data repository.

Costing data for the intervention will be collected utilizing a “top-down” method, as described by the Joint Learning Network [85]. This method will document direct and indirect costs associated with the NCD care delivery intervention described here, and related administrative functions (including planning and administration; training; supervision and monitoring and evaluation; data management; and continuous surveillance) will be disaggregated. Full methodology of direct and indirect costs is provided by the Joint Learning Network [85], and will be utilized for this study. For the purposes of this pragmatic study, this methodology will be appropriate to estimate the additional marginal costs of the intervention (rather than cost-savings or secondary cost implications) as compared to general standard of care.

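### The blood pressure at-goal criterion may be a tailored goal on open-ended grounds, and nothing requires the same goal to score baseline and month 12

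*Protocol article*

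**What the plan says.** Study outcomes, Table 2, counts a hypertensive patient as at goal on "Blood pressure < 130/80 mmHg or patient-tailored goal per risk stratification". Footnote b makes the fixed threshold the default and allows tailored goals for patients aged 65 or over and for those with "multiple comorbidities, limited life expectancy, clinical judgment, patient preference". It gives no numeric limit for a tailored goal and no time at which it is set. It does not say that one goal serves both visits.

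For diabetes, Table 2 gives "Hemoglobin A1c < 7.5 OR fasting blood sugar < 130 mg/dl". It has no rule for results that disagree and does not require the same test at both visits.

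The Sampling strategy section names as primary outcome "the proportion of patients who achieve their NCD control target" after 12 months in care, and bases power on patients whose status changes in either direction between baseline and follow-up. Study design assesses outcomes "after 12 months of being enrolled in NCD care using a pre–post design across both sites", and says of a comparator: "It is not feasible nor ethically acceptable to obtain data on a comparison (control) group in this population". The Quantitative data section takes outcomes from routine records: "Quantitative data for patient outcomes will be extracted from the facility-based EHR and the CHW’s mobile-phone application".

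**The concern.** A paired before-after comparison of a yes/no status can be interpreted only if the same criterion scores both occasions. If a tailored goal is first recorded, or altered, after the enrolment visit, a patient can move from not at goal to at goal, or the reverse, at an unchanged pressure. A control group would show how much of the shift came from such re-scoring; here there is none. Two of the grounds in footnote b, clinical judgment and patient preference, have no objective limit and go beyond the risk stratification that Table 2 itself names.

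What is at stake is whether a rise in the at-goal proportion can be read as better blood pressure control. The diabetes rule raises a smaller question of the same kind: a patient may be scored on one test at baseline and on another, or on both, at month 12.

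**Working it through.** **The plan's own power figure.** The inputs, from the Sampling strategy section, are N = 1000, two-sided alpha 0.05, a net difference d = 0.05, and a discordant proportion pd of 0.40 or 0.10. The formula is power = Φ((√N·d − 1.96·√pd) / √(pd − d²)).
- pd = 0.40: (1.581 − 1.240)/0.630 = 0.54, giving 70.6%. The exact conditional version gives 69.0%; the plan states 69%.
- pd = 0.10: 99.9%; the plan states 99%.

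The power figures are not in dispute.

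**Blood pressure illustration.** The distribution is assumed, because the documents give none: systolic pressure normal with mean 138 and SD 18, unchanged over time, diastolic ignored.
- Share between 130 and 140: Φ((140 − 138)/18) − Φ((130 − 138)/18) = 0.544 − 0.328 = 0.216.
- Goal loosened by 10 mmHg after baseline in 30% of hypertensive patients (assumed): 0.30 × 0.216 = 0.065, or 6.5 points among hypertensive patients.
- If half the cohort is hypertensive (assumed): 0.5 × 6.5 = 3.2 points in the whole cohort.
- Range: with mean 140 to 150 and SD 15 to 18, the share between 130 and 140 is 15.6% to 24.8%. The same 30% then gives 4.7 to 7.4 points among hypertensive patients, or 2.3 to 3.7 points overall.

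**Effect on the test.** Suppose control is truly unchanged, symmetric background discordance is b, and an extra share r of the whole cohort moves to at goal only through re-scoring. Put pd = b + r and d = r in the formula above, with N = 1000. For r = 0.03 and b = 0.40: (0.949 − 1.285)/0.655 = −0.51, giving 30%. For r = 0.03 and b = 0.10: (0.949 − 0.707)/0.359 = 0.67, giving 75%.

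| Drift r | Significant, b = 40% | Significant, b = 10% |
|---|---|---|
| 1 point | 8% | 16% |
| 2 points | 16% | 45% |
| 3 points | 30% | 75% |

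With no drift the rate is the nominal 5%.

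**Diabetes illustration.** Assume each test is passed by 40% of patients. The chance of passing at least one is 0.40 + 0.40 − P(both), which is 54%, 52% and 50% at latent correlations of 0.6, 0.7 and 0.8. The gain of 10 to 14 points over a single test arises only in patients who have one test at baseline and both at month 12. If 30% of diabetic patients do, and diabetes is 30% of the cohort (both assumed), the whole-cohort effect is 0.3 × 0.3 × (10 to 14), or about 1 point.

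**The case against.** The strongest objection is that movement of the goal is inferred from silence. No sentence says that goals change between visits, when they are set, or who sets them. A reader might infer that the staff delivering the intervention will relax goals after baseline; the document does not say so. Three of the footnote's grounds (age, comorbidities, limited life expectancy) would mostly be known at enrolment and apply at both visits. The article is condensed, and an additional file not shown may define the tailored goals. This stands as a limit on the claim. It does not remove the point, because Table 2 and its footnote are the stated definition of the primary endpoint, and as written they permit a different goal at each visit.

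A reader might also infer a one-directional bias. That is not supported: a goal could be tightened after baseline, and the mix of diabetes tests could shift either way.

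Nor do the figures show a bias as large as the effect sought. The 5-point difference used for power and the hypothesised 10% (read here as points) refer to the combined cohort, whereas 6.5 points applies to hypertensive patients only. With half the cohort hypertensive, reaching 5 points overall needs 0.05/(0.5 × 0.216) = 46% of hypertensive patients relaxed after baseline; 10 points needs 93%. At 5% relaxed, the gain among hypertensive patients is about 1.1 points. The illustration also ignores the diastolic limit that Table 2 requires.

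On diabetes, reading the rule as whichever test passes is tempting. Table 2's metric column, which lists the two tests as alternatives, equally supports whichever test was done. Applied to the same tests at both visits, the rule changes the level of at-goal but does not move the yardstick.

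Per-condition rates are planned as secondary outcomes, so a rise confined to hypertension would be visible, though not its cause.

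**Conclusion.** The point holds for blood pressure. An uncontrolled paired comparison rests on a criterion that may be individual, may rest on open-ended grounds, and is not required to be the same at both visits. Whether drift occurs, and in which direction, cannot be known from the document; relaxation would inflate the effect. Under the stated assumptions a plausible size is about 3 points in the whole cohort. That is below the 5 points used for power, yet enough to raise the false-positive rate from 5% to between 30% and 75%. These are illustrations, not estimates for this cohort. The diabetes point is secondary, since it biases change only if the tests done differ between visits. The stated power is sound, and no view is taken on which blood pressure goal is right for care.

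**What to change.** For analysis only, leaving every clinical goal as it is:
- State in footnote b that both visits are scored against the goal recorded at enrolment, or against the Table 2 default where none is recorded.
- Add a sensitivity analysis applying the Table 2 default of < 130/80 mmHg to all hypertensive patients at both visits.
- For diabetes, keep all pairs in the primary analysis and add a sensitivity analysis restricted to patients with the same test at both visits.

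The cost is some footnote wording and extraction of the enrolment goal from the electronic record. The same-test diabetes analysis will have fewer pairs, which is why it is proposed as a sensitivity analysis and not as the primary one.
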